### Measures

#### Primary outcome measures

Substance use behavior will be assessed at baseline, exit, and 90-day follow-up as required by SAMHSA’s Center for Substance Abuse Prevention (CSAP) Government Performance and Results Act (GPRA) adult questionnaire [57]. This includes a measure of frequency of self-reported past 30-day use for days drinking alcohol, binge drinking (as defined by five or more alcoholic beverages at the same time for males; four or more for females), use of various tobacco products (i.e., cigarettes, pipe tobacco, chewing tobacco, snus), electronic vaping, marijuana use, and non-prescribed prescription drug use (i.e., stimulants, sedatives, benzodiazepines, and prescription opioids). Additionally, past 30-day use of illicit drugs, including non-prescription opioids (i.e., cocaine, amphetamines, MDMA/Ecstasy, heroin, fentanyl, etc.) are assessed. Participants indicate the frequency of use on a continuous scale from ‘0’ to ‘30’ days.

Behavioral intent will be examined across all three time points with three items: intent to smoke marijuana/cigarettes, binge drink, and use non-prescribed drugs. Participants are asked to rate the likelihood of use in the next 30 days on a four-point Likert scale from 1 = v*ery likely to* 4 *= very unlikely*. A measure of substance use intention is necessary to determine the effectiveness of the web-app intervention on preventing or reducing participants’ intent to use; and is commonly used in behavior change theory research to determine actual use [58, 59].

#### Alcohol-specific outcomes

As the most frequently used substance among college students [60], ten measures will assess alcohol-related problems at baseline, exit and follow-up adapted from the Rutgers Alcohol Problem Index (RAPI) [61, 62]. Participants who report any past 30-day alcohol use indicate how many times they have experienced ten select outcomes in the last 30 days while drinking alcohol, or as the result of their alcohol use. Example items include: ‘Not being able to do your homework or study for a test’, ‘Missed out on other things because you spent too much money on alcohol’, ‘Went to work or school high or drunk’, ‘Felt that you needed more alcohol than you used to use in order to get the same effect’, and ‘Had withdrawal symptoms, that is, felt sick because you stopped or cut down on drinking’. Participants respond: *never, 1–2 times, 3–5 times, 6–10 times*, and *more than 10 times* in the past 30 days. Prior studies have demonstrated the ability of RAPI to detect DSM-5 AUDs among college students [63], and support its use in the present intervention to determine whether the web-app intervention reduces such negative outcomes at exit and 90-day follow-up compared to those in control and comparison groups.

#### Theoretical construct variables

In accordance with our theory constructs and behavior change strategies (see Table 1), assessment items also include psychosocial correlates that may predict intention to reduce or prevent substance use, such as knowledge, attitudes, risk perception, subjective norms, and self-efficacy*.*

**Attitudes/Knowledge**: To measure retention of substance-related knowledge in pre-, post-test and follow-up surveys, eight items related to potency, lawful use of substances, and risky or harmful use will be examined. These questions directly relate to information presented in the web-application and are intended to determine whether those in the intervention group learn and retain substance-related knowledge significantly more so than those in comparison group and the control group who may receive information in other settings or standardized prevention education on campus. Each item will be scored 1 = correct and 0 = incorrect, and a total knowledge score will be computed with a range between 0 and 8.

**Risk perceptions**: Participants will evaluate their perceived risk level across all three surveys as part of SAMHSA’s CSAP GPRA adult questionnaire [57], for the following six substance use behaviors: binge drinking once or twice a week, tobacco use once or twice a week, marijuana use once or twice a week, prescription opioid use once or twice a week, non-prescription opioid use once or twice a week, sharing needles/injection equipment, injecting drugs, and illicit drug use. Response options for each behavior include 1 = *no risk, 2 = slight risk, 3 = moderate risk, 4 = great risk, or 9 = don’t know.* This measure has been used in prior research to assess misperceptions of risk [64], and aligns with the construct of perceived susceptibility to identify risky behavior. Young adults who perceive themselves to be at moderate or high risk for harm from substance use are significantly less likely to report intention to use substances than those who report no or slight risk [64, 65]. Thus, providing college students with relevant, accurate, and reliable information about the risks and harms associated with substance use can significantly contribute to the prevention or reduction of such use.

**Subjective norms**: Normative re-education will be measured by assessing perceived prevalence of peer substance use at pre-, post-test, and follow-up. Participants indicate what percentage of students on campus they perceive use a variety of substances within the last 30 days, (i.e., alcohol, cigarettes, marijuana, different prescription drugs, and several illicit drugs) choosing one of ten percentile intervals from 0 to 100%. Prior research demonstrates that individuals who recognize peer use to be lower than originally perceived, are less likely to use substances when seeking peer approval [66, 67]. This measure is beneficial to examining the effectiveness of the behavior change strategy of normative re-education among those in the web-app intervention group, and whether such an approach significantly contributes to substance prevention over time.

**Self-efficacy***:* Self-efficacy will be evaluated through two refusal skills statements: “I would be able to say no if a friend offered me a drink of alcohol” and “I would be able to refuse if a friend offered me drugs, including marijuana” [68], by indicating their level of agreement on a four-point Likert scale from 1 = *strongly agree to 4* = *strongly disagree.* These measures are adapted from SAMHSA’s CSAP GPRA youth questionnaire, and are intended to determine whether participants exposed to the web-app report an increase in confidence to refuse substances over time more so than those in the comparison or control conditions. Prior studies suggest the inclusion of substance-related refusal skills measures are a beneficial tool in assessing self-efficacy, and such skills are effective in supporting the prevention or reduction of risky use [69, 70].

#### Other measurements for explorative research

**Socio-demographics***:* Participant characteristics, including age, Hispanic origin, race, sex at birth, gender identification, sexual orientation, living situation, college status, military service/veteran status, arrest history, parole/probation status, and household income will be assessed per SAMHSA’s GPRA adult questionnaire [57].

**Adverse Childhood Experiences (ACE):** At baseline, the ACE questionnaire will be used to measures ten traumatic or stressful childhood events experienced before the age of 18. ACE are conceptualized as maltreatment (e.g., verbal, emotional, physical, and sexual abuse), and household dysfunction (e.g., parent/caregiver substance use, intimate partner violence, incarceration, homelessness, mental illness, separation/divorce) [71]. Participants respond to each of the ten ACE items as 1 = Yes or 0 = No. An ACE score will be computed with a range from 0 to 10. Research has shown that ACE are among the most robust predictors of risky substance use behaviors, including early onset drinking and illicit drug use and prescription drug misuse among college students [72, 73] and that the negative consequences of ACE can vary by ethnicity and gender [74, 75].

**Developmental transition***:* Stressors typically experienced by young adults [76] and associated with substance use [77, 78] will also be explored. At baseline, participants respond 1 = Yes or 0 = No to a list of 18 major life events within the last three years. Example life events include: getting into a new romantic relationship; breaking up with a girlfriend or boyfriend; losing a job; being unemployed and not able to find work; caring for a parent or relative; getting extremely ill; having a baby; losing a baby; or having family separated due to immigration [76]. A total score will be computed with a range from 0 to 18.

### Data management and analysis

All data is collected online using Qualtrics, a fully HIPAA compliant software licensed by the university [79]. To assess program effects within prevention group students, we will calculate Cohen’s *d* to describe the magnitude and direction of the effect size. To examine program outcomes (e.g., alcohol, marijuana, and nicotine use etc.) over time, we will use statistical approaches that account for repeated measures nested within students, determine if longitudinal outcome trajectories are linear or quadratic and identify patterns of stability and change in outcomes over the study period using appropriate modeling approaches. Prevention, comparison, and control students will participate for three waves of data collection. To test whether prevention app participants have no or slower rates of growth in substance use relative to comparison or control students, two level models will estimate two regression equations simultaneously [a within-person equation (i.e., time-level model) and a between-person equation]. This will determine whether the slopes of substance use are less steep among prevention participants than comparison and control group students.

Generalized linear models will also test hypotheses that growth in mediators, for example increases in *knowledge*, will predict flat or slower increases in *substance use*, by including *knowledge* as a time-varying variable in the within-person model. Including individuals’ mean *knowledge* in the between-person intercept equation, and by group-mean centering the *knowledge* within the time-level equations, analyses separate out between-person differences, allowing for an assessment of within-student change in *knowledge* and its relation to *substance use* within the study period. This analytic approach can account for stable, between-student differences and potential bias associated with unmeasured, between-person factors that influence outcome behaviors [80, 81].

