There is a strong link between Healthy People (HP) 2030’s focus on reducing substance use among young people and the need to develop, test, scale, and sustain evidence-based programs. Especially programs designed to limit engagement in health-compromising behaviors, such as substance use; and prevent progression to risky use in service or educational systems. Importantly, HP 2030 identified the following primary public health objectives: reduce a) the number of adults who use marijuana daily or almost daily, b) the proportion of adults who use drugs in the last month, c) the number of people who misuse prescription drugs and, d) the number of young adults who binge drink; goals this study aims to address [32]. This paper describes the rationale, intervention design, and evaluation of the web-app iSTART (initiative for Services in Tech-Health and Rapid Testing) to prevent substance use (i.e., alcohol, marijuana, nicotine, prescription drugs, and illicit drugs) among college students at a Hispanic Serving Institution. We hypothesize that the intervention will prevent increases, limit, or lower substance use (i.e., measured by baseline, 30-day and 90-day binge drinking, marijuana use, etc.) compared to comparison and control groups. We anticipate that the increases in 1) substance-related knowledge, 2) perceived health risk associated with substance use, 3) confidence in refusal skills, and 4) correcting perceptions of substance use prevalence are the mechanisms that reduce and limit substance use behaviors of students in the prevention condition.

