### Study population and recruitment

The study population will consist of college students age 18–30. We will recruit 200 students in the prevention condition, 200 students in the comparison group condition, and 200 students in the matched control condition. We will use mixed models with a random effect for individual to test for the difference in longitudinal slopes with days drinking and marijuana use (example outcomes). We assume an average of 3 measurements per person and a correlation of 0.10 among intra-individual measurements, using a 2-sided test with alpha = 0.05 and 80% power, we will be able to detect a difference in frequency of alcohol and marijuana use at the final endpoint for prevention vs. control and for prevention vs. comparison group with Cohen’s d effect sizes of approximately 0.20 and 0.23, respectively, meaning we will be able to detect small minimum effect sizes among groups. Power analysis indicate that to detect a small effect size, adjusted for covariates across groups (all three groups: control, comparison, and prevention intervention), a minimum of 525 participants are needed over three years. An oversampling of 15% will be conducted to account for possible attrition across surveys. A total sample of 690 college students (evenly randomized to control, comparison, and intervention groups) will be recruited over three years to achieve sufficient statistical power.

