Recruitment of student participants will include printed flyers with study information available on campus during tabling events for students at the beginning of the academic term, during campus events (both in-person and virtual) with different campus organizations; posters on lawn signs, campus buildings, and businesses; and electronic posting on digital campus billboards. Students will be invited to participate via email recruitment fliers to Student Housing and through college and department announcements. All recruitment materials will include the intervention website information, where students can review the study requirements, check their eligibility, and enroll in the study. Initial screening of participants includes an electronic review of study objectives, completion of a brief questionnaire for alcohol use disorder (AUD) or substance use disorder (SUD) risk [based on the Diagnostic and Statistical Manual of Mental Disorders, Fifth Edition (DSM-5) criteria], and electronic consent. Exclusion criteria include: individuals who are not college students, under 18 or over 30 years of age, or at high risk for AUD or SUD. Students screened as high risk for AUD or SUD will be referred to additional resources and excluded from the study.

The study adheres to the Belmont Report Ethical Principles and Guidelines for the Protection of Human Subjects of Research. Approval for the intervention study was provided by the Institutional Review Board.

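### The only effect size named in the analysis section is a Cohen's d within the prevention arm, which cannot separate the app's effect from change common to all arms

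*Protocol article*

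**What the plan says.** Under Data management and analysis, the protocol article introduces its effect size with "To assess program effects within prevention group students, we will calculate" Cohen's d, whose purpose is "to describe the magnitude and direction of the effect size". No other effect size is named in that section.

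The same paragraph then sets out the hypothesis test, a two-level model: "To test whether prevention app participants have no or slower rates of growth in substance use relative to comparison or control students". Its result is read as follows: "This will determine whether the slopes of substance use are less steep among prevention participants than comparison and control group students".

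Study population and recruitment plans the same kind of contrast ("We will use mixed models with a random effect for individual to test for the difference in longitudinal slopes") and quotes detectable d values of about 0.20 against control and 0.23 against comparison. Allocation is described as "evenly randomized to control, comparison, and intervention groups". The Background states the aim comparatively, against both other groups: "We hypothesize that the intervention will prevent increases, limit, or lower substance use".

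On entry to the study: "Students screened as high risk for AUD or SUD will be referred to additional resources and excluded from the study".

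**The concern.** Calling a one-arm change a program effect credits the app with everything that happened between the surveys. Three sources of change would affect all arms alike: ordinary change in use over time, the effect of answering the same questions repeatedly, and regression to the mean after students at high risk have been screened out. The last of these, if present, would push use upward, against the app.

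The mismatch with the trial's own idea of success is sharper. Success means growth that is slower than in the other arms, or absent. Slower growth is still growth, so the direction of a within-arm d need not be the direction of the effect. At stake is whether the reported magnitude and sign describe what the randomised comparison estimates.

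**Working it through.** **Inputs.** From the protocol article: three arms with even randomisation, three survey waves, between-arm planning d of 0.20 and 0.23, assumed intra-individual correlation 0.10, and exclusion of high-risk students by a brief DSM-5 screener completed before the baseline survey. The article gives no figure for the within-arm d, so there is none to reproduce. The d is read here as change from baseline within the prevention arm, the natural meaning of an effect computed in one group over time. For the between-arm planning values, (1.960 + 0.842) × √(2V/200) gives 0.177 with V = (1 + 2 × 0.10)/3 = 0.40 (mean of three measures) and 0.280 with V = 1 (endpoint only). Neither gives 0.20 or 0.23, but that is a separate matter and does not bear on this point.

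**Step 1: what each d estimates.** Let T be the change common to all arms and A the change caused by the app, both in baseline SD units, with negative values meaning less use.

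- Within-arm d = T + A
- Between-arm d = (T + A) − T = A

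**Step 2: consequences.** T is assumed purely for illustration; A is set to zero or to the size of the smaller planning value.

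| T (assumed) | A | Within-arm d | Between-arm d |
|---|---|---|---|
| +0.20 | −0.20 | 0.00 | −0.20 |
| +0.30 | −0.20 | +0.10 | −0.20 |
| −0.20 | 0 | −0.20 | 0.00 |

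In the first two rows a working app shows nothing, or apparent harm. In the third an inert app shows an apparent benefit. A simulation with 200 per arm, no app effect and assumed common drifts of 0, −0.1, −0.2 and −0.3 SD gave the same picture: the within-arm d averaged the drift itself, and the between-arm d averaged 0.00 throughout.

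**Step 3: can T be sized from the document?** Take regression to the mean after the screen. Let r_B and r_F be the correlations of the screening score with use at baseline and at follow-up. Excluding everyone above a cut c gives

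drift = (r_F − r_B) × E[z | z < c], where E[z | z < c] = −φ(c)/(proportion kept).

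If 20% were excluded (assumed), c = 0.842, φ(c) = 0.280 and E = −0.280/0.80 = −0.35.

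| r_B | r_F | Drift (SD) |
|---|---|---|
| 0.6 | 0.6 | 0.00 |
| 0.7 | 0.6 | 0.035 |
| 0.7 | 0.5 | 0.07 |
| 1 (screener is the baseline outcome) | 0.6 | 0.14 |
| 1 | 0.10 (the plan's intra-individual correlation) | 0.315 |

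At one assumed exclusion rate the drift runs from nothing to 0.315 SD. The larger values require the screener to be the baseline outcome, which it is not: screening uses a DSM-5 risk questionnaire, and the outcome is days of use out of 30. The article gives neither the exclusion rate nor these correlations, and it puts no size on time trends or survey effects. The direction of this one component is clear; the size of T is unknown.

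**The case against.** The strongest reply is that the randomised controls are in use where it counts. The slope models compare prevention with both other groups, the power statement is built on that contrast, and the d is described as descriptive, with no test, alpha or decision rule. All of this stands. A reader might infer from the sentence about program effects that the trial measures its effect by a one-arm d and discards its controls. The document does not support that reading: only this one number leaves the controls out.

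A reader might also infer a definite bias comparable to the 0.20 to 0.23 planning effects, or that recruitment is concentrated at the start of term. Neither is supported. The first depends on treating the screener as the baseline outcome. On the second, start-of-term tabling is one of several recruitment routes, and recruitment runs over three years.

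Two lesser replies remain. The choice of SD for the d is a detail commonly left to an analysis plan, and its absence is not held against the article. Differences at two visits are not the same quantity as a slope difference. They can, however, be obtained as contrasts from the same fitted model, and the power statement itself speaks of a difference at the final endpoint.

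None of these replies rescues the label. The article does not leave the effect size open: it names one, calls it a program effect and computes it in a single arm.

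**Conclusion.** The concern holds as a reporting and labelling fault in the named effect size, not as a loss of the randomised comparison. The one-arm d carries any change common to all arms one for one. Given the trial's definition of success, it can therefore misstate both the magnitude and the direction it is meant to describe. This follows from the article's own statements and rests on one reading, that the d is a change over time within the prevention arm. No numerical size is claimed for the bias, because the document does not give the quantities needed; the figures above show only how the quantity behaves under stated assumptions. It should be corrected before analysis, and it does not threaten the validity of the planned hypothesis test.

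**What to change.** Report the effect size as the standardised between-arm difference, for prevention vs control and for prevention vs comparison, each with a 95% CI. Take the differences from the planned mixed model at exit and at 90-day follow-up, and divide by the pooled baseline SD. Keep the slope contrast as the test of the hypothesis.

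Relabel the within-arm d as descriptive change from baseline, and show it for all three arms side by side so that the common change is visible.

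The cost is a change of wording in the analysis section. No extra data, visits or participants are needed. Data collection is already under way, so the change should be recorded before the analysis is run.

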#### Randomization

The web-app is designed to randomize participants to intervention, comparison, or control groups. Upon first login, each participant is automatically randomized into one of the three conditions, and is provided access to the appropriate web-modules: the five weekly substance-specific modules for the intervention group, the single abbreviated module if in the comparison group, or no access to modules if in the control group. The web-application is also designed to keep track of completion dates, or non-completion, and send out automatic reminder emails and new module availability messages to participants.

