#### Incentives

Incentives are provided to ensure participation and retention. Participants receive Amazon.com gift cards via email when they complete pre- and post-test surveys and web-app modules. Exit surveys are auto-administered via email from the web-app. The follow-up survey is emailed by study staff to participants 90 days after exit surveys are completed. Participants have two weeks to complete exit and 90-day follow-up surveys. Those in the intervention group receive a total of $100**:** $15 for baseline, $15 for modules 1 and 2, $15 for modules 3 and 4, $25 for module 5 and the exit survey, and $30 for the 90-day follow-up survey. Comparison group participants receive a total of $75: $15 for baseline, $15 for the single module, $15 for the exit survey, and $30 for the 90-day follow-up survey. The control group receives a total of $65: $15 for baseline, $20 for the exit survey, and $30 for the 90-day follow-up survey.

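### The arm test is a difference in slopes with baseline as the first response and no common baseline mean stated; in its usual form it loses about 18 to 23 points of power at the plan's own correlation of 0.10

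*Protocol article*

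**What the plan says.** Study population and recruitment sets the test: "We will use mixed models with a random effect for individual to test for the difference in longitudinal slopes". On the repeated measurements it says: "We assume an average of 3 measurements per person and a correlation of 0.10 among intra-individual measurements". The other inputs are a two-sided 5% significance level, a power of 80%, and 200 students per arm. It reports detectable effects of about d = 0.20 (prevention vs control) and 0.23 (prevention vs comparison) at the final endpoint.

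Data management and analysis repeats the approach: "two level models will estimate two regression equations simultaneously", one within person and one between persons, followed by "This will determine whether the slopes of substance use are less steep among prevention participants than comparison and control group students".

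Primary outcome measures fixes the waves: "Substance use behavior will be assessed at baseline, exit, and 90-day follow-up". Three waves and three measurements per person make baseline one of the responses. Incentives dates the last wave: "The follow-up survey is emailed by study staff to participants 90 days after exit surveys are completed", so at about day 120.

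No section says whether arm enters the intercept equation, and none names baseline use as a covariate. Covariate adjustment is mentioned once, in the separate sentence deriving the minimum of 525 participants, and the covariates are not named.

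On timing, Eligibility has students complete the baseline survey before they are added to the app, and Randomization adds: "Upon first login, each participant is automatically randomized into one of the three conditions". Study design and setting instead places the baseline survey after assignment to condition, and Study population and recruitment calls the control condition matched.

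**The concern.** In the usual two-level growth model, arm predicts both the intercept and the slope, so each arm has its own baseline mean. The slope difference is then a change-type contrast: it subtracts the observed baseline difference between arms in full, however weakly baseline predicts later use. If baseline precedes randomisation, the true baseline means are equal, and estimating one per arm only adds variance. At a correlation of 0.10 the added variance is large.

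At stake is the precision of the trial's main question, whether the app slows growth in use, in both prevention contrasts. A small true effect, the kind the trial is sized for, would be missed more often than the data already being collected require.

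**Working it through.** **Inputs.** n = 200 per arm, three waves, correlation rho = 0.10, two-sided alpha 0.05 (all from Study population and recruitment). Effect d is the arm difference at the last wave in SD units, growing linearly from zero. Assumed: Gaussian outcome, unit variance, compound symmetry (implied by a single random effect per student), complete data. Time is coded either by wave (0, 1, 2) or by day (0, 30, 120).

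**Formulas.** Write the variance of the arm difference at the last wave as c/n. Power = Phi(d/SE - 1.96) plus a negligible lower tail, with SE = sqrt(c/n). The effect detectable with 80% power is 2.80 x SE.

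1. *Slope model, arm in intercept and slope.* c = 2(1 - rho) x T^2/Sxx, where T is the last time and Sxx the sum of squared deviations of the times.
   - Waves: T^2/Sxx = 4/2 = 2, so c = 2 x 0.9 x 2 = 3.60.
   - Days: mean 50, Sxx = 2500 + 400 + 4900 = 7800, T^2/Sxx = 14400/7800 = 1.846, so c = 3.32.
2. *90-day comparison adjusted for baseline.* c = 2(1 - rho^2) = 1.98.
3. *Slope model, common baseline mean.* c = 2/(t'V^-1 t), with t scaled to end at 1 and t'V^-1 t = [sum t^2 - (rho/(1 + 2 rho))(sum t)^2]/(1 - rho).
   - Waves: [1.25 - 0.0833 x 2.25]/0.9 = 1.181, so c = 1.69.
   - Days: [1.0625 - 0.0833 x 1.5625]/0.9 = 1.036, so c = 1.93.
4. *90-day value alone.* c = 2.

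**The plan's own figure.** The stated 0.20 and 0.23 are not reproduced. At n = 200 the slope test detects 0.376 (waves) or 0.361 (days), the adjusted 90-day comparison 0.279, the mean of the two post-baseline waves 0.208, and the mean of all three waves 0.177. Two contrasts of equal size and equal inputs also cannot have two different detectable effects.

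**Power, n = 200 per arm, rho = 0.10**

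| Test | c | d = 0.20 | d = 0.23 |
|---|---|---|---|
| Slope, free arm baselines, waves | 3.60 | 32% | 40% |
| Slope, free arm baselines, days | 3.32 | 34% | 43% |
| 90-day value alone | 2.00 | 51.6% | 63.3% |
| 90-day value, baseline-adjusted | 1.98 | 52.0% | 63.7% |
| Slope, common baseline, days | 1.93 | 53% | 65% |
| Slope, common baseline, waves | 1.69 | 58% | 71% |

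The adjusted 90-day comparison gains 20 points (waves) or 18 (days) at d = 0.20, and 23 or 21 at d = 0.23. At the other arm sizes the article implies, the d = 0.20 wave-coded gain is 18 points at 525/3 = 175 and 22 at 690/3 = 230.

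**Cause.** The 90-day value alone already reaches 51.6%; baseline as a covariate adds 0.4 points. The loss is the cost of subtracting a weakly correlated baseline.

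**Other correlations (assumed), d = 0.23, free-baseline slope vs adjusted 90-day comparison**

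| rho | Slope, waves | Slope, days | Adjusted | Gain |
|---|---|---|---|---|
| 0.3 | 49% | 53% | 67% | 15-18 points |
| 0.5 | 63% | 67% | 76% | 9-12 points |
| 0.7 | 84% | 87% | 90% | 3-5 points |

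**The case against.** The strongest reply is that the model that loses power is inferred. The article never says that arm enters the intercept equation, it leaves the trajectory form open, and a condensed article may leave exact fixed effects to a fuller plan. This stands in part. A reader might infer that the plan rules out baseline adjustment; the text supports only that none is stated. If arm enters only the slope equation, the loss does not arise, and one sentence would settle the matter. But the slope contrast over three waves, with baseline as a response, is a stated choice and not a missing detail. The unnamed covariates do not repair it either: adding baseline as a covariate while it remains a response would not recover the loss.

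A second reply is that growth is a legitimate question and a single 90-day contrast is a different one. This is right, and it favours the common-baseline slope model, which keeps the growth question. The power statement itself, however, speaks of a difference at the final endpoint.

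A third is that the size hangs on a planning correlation. It does. A reader might also infer that the adjusted 90-day comparison always wins. With day coding it does not: per student and arm, 1.846(1 - rho) - (1 - rho^2) = (1 - rho)(0.846 - rho), which turns negative above a correlation of about 0.85, far from 0.10.

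Finally, a reader might infer that chance baseline imbalance biases the slope test. It does not across randomisations; the standard error covers it. The issue is precision.

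**Conclusion.** The point holds conditionally. If arm has its own intercept, the stated slope test has about 32-34% power at d = 0.20 and 40-43% at d = 0.23, and 18 to 23 points are recoverable from data already collected by the adjusted 90-day comparison. The common-baseline slope model recovers as much or more.

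This rests on the usual form of the model, the plan's correlation of 0.10, 200 per arm with complete data, a Gaussian outcome and compound symmetry. The outcomes are counts of 0 to 30 days, some for rarely used drugs, so the figures should not be carried over to every outcome.

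Two stronger conclusions do not follow. Baseline is not an important omitted predictor at this correlation. Nor does the change rescue the stated power: the best figures in the first power table are 58% and 71%, still short of 80%.

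Both remedies also presuppose a baseline taken before randomisation. Eligibility and Randomization support that; Study design and setting contradicts it.

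**What to change.** In Study population and recruitment and in Data management and analysis, state how baseline enters the arm comparison.

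- *Preferred:* keep the three-wave slope model but constrain the arms to a common baseline mean, with no arm main effect and arm-by-time terms only. This keeps the growth question and every student.
- *Alternative:* take exit and 90-day use as responses, with baseline use of the same substance as a covariate and arm-by-wave terms. This drops students with no post-baseline survey, which is not trivial when 15% attrition is planned for, and replaces the growth rate with an adjusted difference.

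Apply the choice to both prevention contrasts and to the use and intent outcomes, with the same linear predictor if a count link is used.

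Reconcile Study design and setting (baseline survey after assignment) and the matched control wording with Eligibility and Randomization (baseline survey before randomisation at first login), and state which survey serves as baseline.

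The cost is wording only: no new data, staff or students. The article reports data collection under way, so the change should be documented before the arms are compared.
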